### Study groups and management

Babies in the placebo group will receive 0.45 % saline through the UAC (standard therapy). Babies in the intervention group will receive an amino acid solution (8.5 % TrophAmine®, B Braun Medical, Irvine, USA) through the UAC giving an extra 1 g.d^-1^ of protein above standard intravenous nutrition. Babies in both groups will receive routine neonatal care including intravenous and enteral nutrition according to each centre’s practice.

### Randomisation

Within 24 h of birth and once a UAC has been placed in an acceptable position, babies will be enrolled by medical and research staff and randomly allocated in a 1:1 ratio to treatment and placebo groups via a web-based interface maintained and concealed by an independent database controller. Twins will be randomised as separate babies. Randomisation will be stratified for recruitment centre (each centre has different nutrition practices), sex and appropriate-for-gestational-age/small-for-gestational-age status (these variables influence growth and body composition), using blocked randomisation with variable block sizes.

### Blinding

Subjects and their families, clinical staff, investigators and assessors at follow up appointments will be blinded to treatment allocation throughout the entire study. Intervention and placebo fluids will be made by an independent contractor and will be identical in appearance and identified only by a randomly generated numerical identifier. Composition of the fluid in each bag will be known only by the independent database controller. Unblinding should occur only in exceptional circumstances when knowledge of the actual treatment is absolutely essential for further management of the patient. If unbinding is deemed to be necessary by a neonatologist, the neonatologist is encouraged to discuss this with the overall responsible investigator ([name]). The actual allocation will not be disclosed to parents and/or other study personnel. Any code break that occurs will be reported to the principal investigator and Steering Group without identifying treatment allocation.

### Intervention

All babies will receive nutrition according to individual neonatal intensive care unit practices. In addition, babies will be randomised to one of two groups:

Treatment group: Babies will receive an infusion of 8.5 % TrophAmine® at 0.5 ml.h^−1^ via the UAC, providing 1 g protein in 12 ml or 1–2 g.kg^−1^.d^−1^ additional protein, depending on birthweight. Placebo group: Babies will receive an infusion of 0.45 % saline at 0.5 ml.h^−1^ via a UAC (current standard practice). Both solutions will contain heparin 0.5 iU.ml^-1^. The intervention will continue for 120 h.

#### Blood sample analysis

Routine biochemical monitoring will take place in accordance with local guidelines. Concentrations of potassium, pH, bicarbonate, base excess and lactate will be recorded daily. In addition, blood samples will be collected on day 1 (24 h after UAC infusion starts) and day 5 (after the UAC study fluids cease) for the measurement of serum concentrations of urea, albumin, total protein, globulin, calcium and phosphate concentrations on days 1 and 5, and ammonia concentration on day 5. Study blood results will not be revealed to attending physicians.

#### Newborn metabolic screening

Blood spots taken for routine Newborn Metabolic Screening will be taken immediately before and after the 5-day intervention period. Consent has been granted by the New Zealand National Screening Unit for access to the Newborn Metabolic Screening data, including amino acid and acyl carnitine concentrations.

#### Monitoring of nutritional intake

Total enteral and intravenous intakes will be recorded daily until day 28. Mean daily protein, energy and other nutrient intakes will be calculated based on actual intakes. Full enteral feeds will be defined as the day when no further intravenous nutrition is given or 150 ml.kg^-1^d^-^^1^ enteral feeds is reached. Energy and protein intakes will be calculated using preterm transitional breast-milk composition for the first 2 weeks (65 kcal and 1.5 g protein.100 ml^−1^) and mature breastmilk composition thereafter (72 kcal and 1.2 g protein.100 ml^−1^) [34–38].

#### Participant withdrawal

Development of significant renal impairment (serum creatinine > 130 μmol.l^−1^) or diagnosis of an inborn error of metabolism requiring prescribed protein intakes will result in the intervention being discontinued. Participants will be withdrawn from the trial at parental request or if the attending physician determines that this is essential for the baby’s care. Consent will be requested to continue to use routinely collected data for study purposes.

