### Trial entry and randomisation

Parents will be given a written information sheet about the study antenatally (where possible), which will be reviewed with them by a member of the study team. If birth occurs without time for this to happen, information will be given to the parents as soon as is feasible after birth and reviewed with them by a member of the study team. Within 24 h of birth and once a UAC has been placed, eligible babies will be randomised to either the placebo group or the intervention group. Babies for whom it was not possible to obtain consent antenatally will be enrolled based on a waiver of consent (approved by the ethics committee) with a requirement that informed, written consent is obtained within 24 h. If consent is not obtained within 24 h of randomisation, the baby will be withdrawn from the study.

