### Study outcomes

#### Primary outcome

The primary outcome will be survival free from any neurodevelopmental disability at 2 years’ corrected age. Assessment will include the Bayley Scales of Infant Development Edition 3 (Bayley III), neurodevelopment, growth and body composition. Cerebral palsy (loss of motor function and abnormalities of muscle tone and power) and other impairment outcomes will be assessed according to previously reported criteria [39]. The severity of gross motor function will be classified using the Gross Motor Function Classification System [40]. Children with severe developmental delay who are unable to complete the psychological assessment will be given a standardised score of - 4 SD. Children will be considered blind if visual acuity in both eyes is worse than 6/60 and deaf if their hearing loss is sufficient to require hearing aid(s), or worse.

Children will be considered to have a neurodevelopmental disability if they have cerebral palsy, a gross motor classification score ≥1 [40], blindness, deafness or developmental delay, defined as a standardised score for cognitive, motor or language scales more than 1 SD below the mean [41]. The neurodevelopmental disabilities imposed by the various neurodevelopmental impairments will be classified as severe, moderate or mild [39].

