##### Statistical analyses

Statistical analyses will be performed on an intention-to-treat basis. Missing outcome data will not be imputed in the primary analysis, as the key assumption of missing at random is not likely to hold in the analysis population. Sensitivity analyses will be conducted, however, using multiple imputations method to explore the potential impact of missing data on outcomes. The characteristics of those participants with missing data will be compared between two treatment groups. Per protocol analysis will be performed for those who received at least 80 % of the intended treatment. Sub-group analysis will be conducted on the treatment outcomes in relation to total protein received and to the extra study dose received. Statistical tests will be two-sided at a 5 % significance level. Twins will be randomised as separate babies, with the non-independence of these pairs taken into account during analysis.

Baseline characteristics of all randomised babies and their mothers will be summarised for each group as well as overall using descriptive statistics. Continuous variables will be reported as numbers of observed and missing values, mean, standard deviation, median and range. Categorical variables will be described as frequencies and percentages. The primary outcome, survival free of disability, will be first presented as unadjusted relative risk (RR) with 95 % confidence interval (CI). Generalised linear regression models appropriate to continuous and categorical outcomes will be used to evaluate the treatment difference between two groups, adjusting for stratification variables and other baseline confounders that are closely associated with the outcomes (e.g. birth weight, sex and treatment with antenatal steroids). Adjusted RRs and 95 % CIs will be estimated using a log link. Analyses of growth outcomes will be performed following completion of NICU discharge assessments but will not be revealed to assessors of the Bayley III at 2 years’ corrected age.

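### Physician-directed withdrawal takes a baby out of the trial rather than off study fluid alone, so survivors may lack the 2-year primary outcome and the intention-to-treat analysis is open to bias

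*Protocol article*

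**What the plan says.** The section on participant withdrawal sets out two routes.

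- **Named triggers.** Serum creatinine above 130 μmol/l, or an inborn error of metabolism "requiring prescribed protein intakes will result in the intervention being discontinued". Nothing there takes the baby out of the trial or out of follow-up.
- **Parent or physician.** "Participants will be withdrawn from the trial at parental request or if the attending physician determines that this is essential" for the baby's care. The section then adds: "Consent will be requested to continue to use routinely collected data for study purposes".

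The section on trial entry and randomisation has a separate rule for babies enrolled under the consent waiver. Without consent within 24 h of randomisation, "the baby will be withdrawn from the study".

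On outcome and analysis:

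- **Outcome.** "The primary outcome will be survival free from any neurodevelopmental disability at 2 years’ corrected age". Its assessment includes Bayley III and a gross motor classification.
- **Principle.** The section on statistical analyses opens with this: "Statistical analyses will be performed on an intention-to-treat basis".
- **Missing outcomes.** The same section rules out imputation at the primary step: "Missing outcome data will not be imputed in the primary analysis, as the key assumption of missing at random is not likely to hold".
- **Sensitivity.** It offers this as the check: "Sensitivity analyses will be conducted, however, using multiple imputations method to explore the potential impact of missing data on outcomes".

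**The concern.** Stopping an infusion and leaving a trial are different events. The withdrawal section keeps them apart for the named triggers but merges them when the attending physician makes the decision, putting that decision on the same footing as a parent's refusal. The only request that follows covers routine data, and the protocol does not say that the 2-year assessment is routine care.

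A physician's judgement of this kind probably follows illness or a suspected effect of the infusion. Missing outcomes on this route are therefore likely to be related to prognosis, and their number could differ by arm if the fluid itself has clinical effects. This is a rule stated in the protocol, not a detail left to an analysis plan. No analysis plan can recover an assessment that was never made.

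**Working it through.** **1. The plan's own figure.** Inputs from the sample size section: 50% v 65%, two-sided 5%, 85% power, 10% loss. With the pooled-variance formula and no continuity correction:

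n = [1.960 × √(2 × 0.575 × 0.425) + 1.036 × √(0.50 × 0.50 + 0.65 × 0.35)]² / 0.15² = 193.5, so 194 per group.

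194 / 0.90 = 215.6, so 216 per group and 432 in total, against the stated 430. The plan's 215 × 0.90 = 193.5 evaluable per group gives 85.0% power. The sample size is sound.

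**2. Effect on power.** The allowance is 0.10 × 215 = 21.5 babies per group, and each 1% withdrawn is 2.15 babies. If physician withdrawals fall within the 10%, power stays at 85.0%. If they come on top of it:

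| Extra loss | Evaluable per group | Power |
|---|---|---|
| 2% | 189.2 | 84.2% |
| 5% | 182.8 | 82.9% |
| 10% | 172.0 | 80.6% |

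**3. Effect on bias.** Let p be the true disability-free survival in the whole arm, w the fraction withdrawn with outcome unknown, and q the rate among those withdrawn. The observed rate is (p − w·q)/(1 − w), so the shift is w(p − q)/(1 − w). The protocol gives neither w nor q, so both are assumed here. Take p = 0.50 in both arms, that is, no treatment effect.

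With w = 0.05 in one arm only and q = 0.25: (0.50 − 0.05 × 0.25)/0.95 = 0.4875/0.95 = 0.513. The other arm shows 0.500, so the spurious difference is 1.3 points.

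Over a range of q from 0 to 0.35:

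| Withdrawn, arm A v arm B | Spurious difference, A − B |
|---|---|
| 5% v 5% | 0 (both arms show 50.8% to 52.6%) |
| 5% v 2% | 0.5 to 1.6 points |
| 10% v 2% | 1.4 to 4.5 points |

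**4. Dependence on known deaths.** Step 3 treats every withdrawn baby's outcome as unknown. If deaths are still learned from routine data, they stay in as failures and only survivors are lost. At the extreme, every failure among the withdrawn is a known death. The missing fraction is then 0.05 × 0.25 = 0.0125, and the observed rate is 0.4875/(1 − 0.0125) = 0.494, a shift of −0.6 points. With these inputs the bias lies between −0.6 and +1.3 points, so even its direction depends on what is retained after withdrawal.

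**5. The protocol's own logic.** A per-protocol analysis is planned for babies who received at least 80% of treatment. Babies who stop early therefore belong in the intention-to-treat set and need outcomes. Children too delayed to be tested are scored at −4 SD, which keeps the worst results in the analysis. The physician route can lose such children before they reach that rule.

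**The case against.** Several stronger readings are tempting, and the protocol does not support them.

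- **All babies taken off for clinical reasons leave the trial.** They do not. The two named triggers only discontinue the intervention. That these are the sickest babies is an inference, not a statement.
- **The 2-year outcome is lost.** It may be. The article does not say that follow-up is barred after withdrawal, nor whether the 2-year assessment counts as routine care, and a death is a failure that routine data may show.
- **Intention-to-treat cannot be done.** It becomes incomplete, not impossible. The plan allows 10% loss, compares babies with missing data between arms and adds multiple imputation. That last safeguard is limited: standard multiple imputation assumes missing at random, which the plan itself doubts.
- **The waiver rule deletes early deaths.** The rule follows from a condition of the ethics approval. The article does not say how a baby who dies before consent is handled, and babies in danger of imminent death are excluded.

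Blinding is the best further argument. Families and clinical staff are blinded, the fluids look identical, and study blood results are withheld from attending physicians. Withdrawal cannot follow known allocation. This makes a large imbalance less likely but does not exclude one. Routine biochemistry continues under local guidelines, so physicians may react to effects of the fluid without knowing the arm.

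What stands is that the physician route ends trial participation and the consent request does not reach the 2-year assessment.

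**Conclusion.** The point holds for physician-directed withdrawal and should be fixed. Surviving babies on this route may lack the primary outcome and drop out of an unimputed analysis described as intention-to-treat, for a reason probably tied to prognosis. The result is an incomplete analysis open to bias.

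The size is unknown because no withdrawal rate is given. Under the main illustration it is about 1.3 points, less than a tenth of the 15-point target (1.3/15 = 0.09). That case puts all withdrawals in one arm and retains none of their outcomes. The widest case shown, 10% v 2% withdrawn with no disability-free survivors among them, gives 4.5 points. The power cost is nil if these losses fall within the 10% allowance.

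**What to change.** 1. Reword the withdrawal section so that a physician's decision to stop study fluid is recorded separately from withdrawal from follow-up. Leave unchanged who decides, and when, that study fluid stops.
2. Keep these babies in data collection, the 2-year assessment and the intention-to-treat set unless parents refuse.
3. Name the 2-year assessment and survival status in the continuing-consent request, alongside routine data.
4. For waiver babies without consent, report numbers by arm, and keep survival status only if the ethics approval allows it.

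The cost is one protocol paragraph, a line in the consent form and a small ethics amendment. The sample size is unaffected. The change is worth making before follow-up is missed, because uncollected outcomes cannot be recovered later.

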### Study outcomes

#### Primary outcome

The primary outcome will be survival free from any neurodevelopmental disability at 2 years’ corrected age. Assessment will include the Bayley Scales of Infant Development Edition 3 (Bayley III), neurodevelopment, growth and body composition. Cerebral palsy (loss of motor function and abnormalities of muscle tone and power) and other impairment outcomes will be assessed according to previously reported criteria [39]. The severity of gross motor function will be classified using the Gross Motor Function Classification System [40]. Children with severe developmental delay who are unable to complete the psychological assessment will be given a standardised score of - 4 SD. Children will be considered blind if visual acuity in both eyes is worse than 6/60 and deaf if their hearing loss is sufficient to require hearing aid(s), or worse.

Children will be considered to have a neurodevelopmental disability if they have cerebral palsy, a gross motor classification score ≥1 [40], blindness, deafness or developmental delay, defined as a standardised score for cognitive, motor or language scales more than 1 SD below the mean [41]. The neurodevelopmental disabilities imposed by the various neurodevelopmental impairments will be classified as severe, moderate or mild [39].

#### Secondary outcomes

##### Growth

Weight, length and head circumference will be measured at birth, 28 days, 8 and 36 weeks’ postmenstrual age, and at discharge. Weight, height and head circumference will be measured at 2 years’ corrected age. All measurements will be by trained staff using validated, repeatable methods [42, 43]. All growth data Z-scores will be calculated individually for each baby using appropriate normative data. Growth velocity (GV) will be calculated using: GV = [1000 × ln(Wn/W1)]/(Dn ‐ D1) where W = weight (g) and D = day after birth on days n (end of time interval) and 1 (beginning of time interval) [44].

##### Body composition

Body composition, where possible, will be measured by air displacement plethysmography at 36 to 42 weeks’ post-menstrual age and at 2 years’ corrected age.

##### Neonatal outcomes

The presence of morbidities at 36 weeks’ post-menstrual age, including intraventricular haemorrhage (IVH), severe IVH (Grade 3 or 4 defined using the grading system from Papile et al. [45]), periventricular leukomalacia, chronic lung disease (need for oxygen at 36 weeks’ post-menstrual age or 28 days after birth if born after 32 weeks’ gestation), retinopathy of prematurity grades 3 and 4 as per the International Classification of Retinopathy of Prematurity [46], necrotising enterocolitis (defined as Bell’s stage 2 or higher [47]), patent ductus arteriosus diagnosed by echocardiography needing treatment, length of NICU stay and late-onset sepsis (beyond 7 days after birth and defined as a positive bacterial culture in cerebrospinal fluid, urine or blood with clinical signs of infection and with antibiotics for 5 or more days with the intention of treating an infection, or treatment for a shorter period if the patient died. If after 10 days of appropriate antibiotic therapy there was demonstration of sterile culture and then the same organism was cultured or if a different organism was cultured from a subsequent culture, this will be considered an additional episode).

##### Nutritional intake

Intravenous and enteral nutritional intake until 28 days (fluid, energy, protein, fat, carbohydrate, vitamins and minerals). Feed type and nutritional supplementation at NICU discharge.

#### Statistical considerations

##### Sample size

A total of 430 babies (*n* = 215 in each group) will provide 85 % power at a 5 % level of significance (two-sided), to detect an absolute difference of 15 % in survival free of disability between the two groups at 2 years’ corrected age. The sample size has taken into account a 10 % loss to follow up rate and a disability rate in the control group of 50 %.

##### Statistical analyses

Statistical analyses will be performed on an intention-to-treat basis. Missing outcome data will not be imputed in the primary analysis, as the key assumption of missing at random is not likely to hold in the analysis population. Sensitivity analyses will be conducted, however, using multiple imputations method to explore the potential impact of missing data on outcomes. The characteristics of those participants with missing data will be compared between two treatment groups. Per protocol analysis will be performed for those who received at least 80 % of the intended treatment. Sub-group analysis will be conducted on the treatment outcomes in relation to total protein received and to the extra study dose received. Statistical tests will be two-sided at a 5 % significance level. Twins will be randomised as separate babies, with the non-independence of these pairs taken into account during analysis.

Baseline characteristics of all randomised babies and their mothers will be summarised for each group as well as overall using descriptive statistics. Continuous variables will be reported as numbers of observed and missing values, mean, standard deviation, median and range. Categorical variables will be described as frequencies and percentages. The primary outcome, survival free of disability, will be first presented as unadjusted relative risk (RR) with 95 % confidence interval (CI). Generalised linear regression models appropriate to continuous and categorical outcomes will be used to evaluate the treatment difference between two groups, adjusting for stratification variables and other baseline confounders that are closely associated with the outcomes (e.g. birth weight, sex and treatment with antenatal steroids). Adjusted RRs and 95 % CIs will be estimated using a log link. Analyses of growth outcomes will be performed following completion of NICU discharge assessments but will not be revealed to assessors of the Bayley III at 2 years’ corrected age.

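### Subgroups by total protein received are partly defined by the allocation itself, so active-versus-placebo comparisons within them are not randomised

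*Protocol article*

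**What the plan says.** The Statistical analyses section commits to this: "Sub-group analysis will be conducted on the treatment outcomes in relation to total protein received and to the extra study dose received". It does not call the analysis exploratory or observational. The main analysis is by intention to treat.

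Three other parts of the article determine what these variables contain.

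- **Allocation.** The Intervention section describes the active infusion as "providing 1 g protein in 12 ml or 1–2" g/kg/d of "additional protein, depending on birthweight". Study groups and management says this is an amount "of protein above standard intravenous nutrition". The placebo is saline and adds none.
- **Background intake.** This is not randomised: "Babies in both groups will receive routine neonatal care including intravenous and enteral nutrition according to each centre’s practice". The Randomisation section gives as its reason for stratifying by centre that "each centre has different nutrition practices". The Background section adds that recommended intakes are hard to reach because fluid volumes are low and drugs and other non-nutritive infusions compete for them.
- **Timing.** Under Monitoring of nutritional intake, "Total enteral and intravenous intakes will be recorded daily until day 28". Under Participant withdrawal, renal impairment or certain inborn errors of metabolism "will result in the intervention being discontinued".

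**The concern.** A subgroup analysis keeps the protection of randomisation only if allocation could not have altered subgroup membership. Total protein received fails that test by design, because the study infusion is one of its components. Within a band of total protein the arms have reached the same total by different routes: active babies with less background nutrition, placebo babies with more. If background nutrition tracks prognosis, the contrast reflects prognosis as well as treatment. The article's own account of competing drug infusions makes such a link plausible.

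The Abstract and Background say that the amount of protein required is unknown. Results by protein received will be read as evidence on exactly that question, and they would carry the confounding of the retrospective data that the trial is meant to improve on.

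**Working it through.** **1. Reproduce the added dose.** Inputs from the Intervention section: an 8.5% solution at 0.5 ml/h.

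- Volume: 0.5 × 24 = 12 ml/d.
- Protein: 12 × 0.085 = 1.02 g/d.
- Per kg: 1.02 / 0.999 = 1.02 g/kg/d at 999 g, and 1.02 / 0.5 = 2.04 g/kg/d at 500 g.

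The article's figures of 1 g and 1–2 g/kg/d reproduce.

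**2. Write down the subgroup variable.** Let T be total protein, B background protein (both g/kg/d), W birthweight in kg, and A = 1 for active and 0 for placebo:

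T = B + A × 1.02 / W

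At a fixed total t, a placebo baby has B = t and an active baby has B = t − 1.02/W. At W = 0.75 kg the gap in background intake is 1.02 / 0.75 = 1.36 g/kg/d. Conditioning on T therefore forces the arms apart on B.

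**3. Size of the false difference when treatment does nothing.** The following inputs are assumptions, because the documents give no values:

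- W uniform on 0.5–1.0 kg.
- B with mean 3 and SD 0.5, 0.7 or 1.0 g/kg/d.
- Correlation r between B and underlying health.
- Survival free of disability at 50% on average, with an odds ratio of 1.5 or 2.7 per SD of health.
- T split at the pooled median.

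With 2,000,000 simulated babies, the active share of the high-protein half is 91%, 83% and 76% for SD 0.5, 0.7 and 1.0, instead of 50%. Active minus placebo, in percentage points (low half / high half):

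| Odds ratio | r | SD 0.5 | SD 0.7 | SD 1.0 |
|---|---|---|---|---|
| 1.5 | 0.3 | -4.0 / -4.7 | -3.2 / -3.6 | -2.3 / -2.6 |
| 1.5 | 0.6 | -8.3 / -9.4 | -6.5 / -7.1 | -4.8 / -5.3 |
| 2.7 | 0.3 | -8.9 / -9.9 | -6.9 / -7.6 | -5.1 / -5.4 |
| 2.7 | 0.6 | -17.6 / -19.6 | -13.8 / -15.0 | -10.3 / -11.0 |

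At r = 0 every difference is within 0.2 points of zero. The whole-trial difference is within 0.1 point of zero throughout. A negative r reverses the sign and gives false benefit.

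**4. False-positive rate.** With 430 × 0.9 = 387 evaluable babies per trial, odds ratio 2.7 and SD 0.7–1.0, a two-sided 5% test within a half rejects about 5% of the time at r = 0, 10–13% at r = 0.3, 18–26% at r = 0.5 and 30–44% at r = 0.7.

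**5. Extra study dose received.** The article does not give the unit, and the problem depends on it.

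- *Grams of study protein:* every placebo baby has zero, so no band above zero has a randomised control.
- *Grams per kg:* the planned dose is 1.02/W, so it largely marks birthweight.
- *Volume or share of study fluid:* this exists in both arms, but depends on survival and on discontinuation after randomisation.

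**The case against.** The article says only that outcomes will be examined in relation to intake. It specifies no bands, no median split and no between-arm test within bands, and a dose-response analysis is a fair alternative reading. This stands as far as the table goes: its figures apply only to between-arm comparisons within bands. It does not rescue the analysis, since a dose-response comparison of babies by what they received is not randomised either.

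The sizes rest on assumed inputs. This also stands. A reader might infer that a false difference of 10 to 20 points is to be expected; the documents do not support that, because they give neither the correlation nor the strength of the link to outcome. Some variation in intake is between centres, and centre, as a stratification variable, is in the adjusted model. The simulation has no centre component and no covariate adjustment, so it may overstate what remains.

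A reader might also infer that study dose is as flawed as total protein, or has no placebo counterpart at all. Both arms receive masked fluid at the same rate for 120 h, and the per-protocol rule of at least 80% of intended treatment can be applied to both. Nor does the link between per-kg dose and birthweight bias the comparison of arms by itself. With no treatment effect and an outcome that depends on birthweight, the arms agree to within 0.1 point inside each third of planned dose per kg.

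Finally, labels and cut-points may be left to a full protocol or analysis plan that is not shown. That covers missing detail, but not the choice of subgroup variable, which the article itself makes.

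**Conclusion.** The point holds for total protein received: the article names a subgroup variable that allocation changes, so comparisons of arms within its bands are not randomised. The imbalance in arm shares (76–91% active in the upper half of a median split) follows from the added dose and an assumed background SD of 0.5–1.0 g/kg/d. The false difference ranges from zero to about -20 points over the assumptions shown. Its upper end exceeds the 15-point effect the trial is sized to detect, but only where intake and prognosis are strongly linked.

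For extra study dose received the point is weaker: it depends on survival and discontinuation after randomisation, and its meaning changes with the unit.

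None of this touches the primary intention-to-treat result, and it should not be read as casting doubt on it. It is a flaw in secondary analyses that is worth correcting, because those analyses bear on the question that motivates the trial.

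**What to change.** Replace the two received-intake subgroups with baseline ones: birthweight band, which sets the planned dose per kg, and recruitment centre, which is already a stratum and stands in for differing nutrition practice. Test each by a treatment-by-subgroup interaction in the intention-to-treat population, allowing for twin pairs as already planned.

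If protein or study dose actually received is still to be analysed, state its unit and label it observational dose-response. Adjust for birthweight, centre and baseline illness, and make no between-arm comparison within received-intake bands. The article names no illness measure, so one recorded before the infusion starts would have to be identified.

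The baseline subgroups need a change of wording and no new data. A subgroup by each centre's standard prescribed protein would need more, because the article says that actual intakes are recorded, not centre prescriptions.

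There are three costs. The trial gives up any subgroup claim about protein actually received. Birthweight and centre differ in more than protein, so an interaction would not isolate a protein effect. Interaction tests are also imprecise: with two equal halves, each half-trial effect has twice the variance of the whole-trial effect, so their difference has 2 + 2 = 4 times that variance and twice its standard error.
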